### Measures

#### Total cost per patient per year

The total cost per patient per year is determined by adding the annual direct medical costs, direct non-medical costs, and indirect costs for each patient. When calculating the cost of the recuperation fee for patients who required nursing care in nursing homes, gerocomiums, or care facilities, 8% of the basic cost is subtracted to reflect the AD patient’s basic cost of living [30]. Two approaches are being used to estimate the monetary loss of informal caregivers. For the informal caregivers who have no stable job before taking care of the AD patients, the average labour market income reported by each research centre is being multiplied by the amount of time spent being a caregiver to obtain the monetary loss. For individuals with a stable job before taking care of the AD patient, the monetary loss is being obtained by multiplying the hourly salary before they stop working by the time spent (hours) being a caregiver. All of the costs will be converted into the average annual cost.

#### Current total number of patients with AD in China

A model is established to estimate the total number of Chinese patients with AD in 2015 based on the literature. The total number of patients with AD is defined as M and the percentage of AD patients who received anti-dementia treatment is defined as d%. Therefore, the number of anti-dementia treated patients (M_1_) is M × d%, and the number of patients not treated for dementia (M_2_) is M × (1–d)%. Based on previous reports, the percentage of AD patients who are treated for dementia is 10–30% [31, 32]. Epidemiological studies have revealed that the number of AD patients in China aged ≥ 60 years in 1990, 2000, and 2010 was 1.93 million, 3.71 million, and 5.69 million, respectively [8, 33, 34]. A linear regression model is used to estimate the age-specific prevalence of AD in 2015 by recording the prevalence of AD among different-aged patients. By multiplying the percentage of AD among elderly individuals aged ≥ 60 years by the total national elderly population (aged ≥ 60 years) in 2015, we obtain the estimated total number of AD patients of China, which is defined as M.

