#### Nationwide cost due to AD

A pilot study is performed, which reveal that the average annual ratio of inpatients to outpatients in different hospitals is ~1:6. Hence, the number of patients who undergo treatment nationwide (M_1_) is multiplied by 1/7 or 6/7 to obtain the number of hospitalised patients with AD (M_1_1_) and the number of outpatients with AD (M_1_2_), respectively. Thus, the total national annual cost of patients who accept treatment is M_1_1_ × F_1_1_ + M_1_2_ × F_1_2_. M_2_ is defined as the number of patients who did not accept treatment, and this value is multiplied by F_2_ to obtain the total annual national cost of patients who do not accept treatment. Therefore, the total annual national cost of patients with AD is M_1_1_ x F_1_1_ + M_1_2_ x F_1_2_ + M_2_ x F_2_. To estimate the costs attributable to AD, generalised linear models (GLMs) related to coexisting conditions (stroke, diabetes, heart disease, hypertension, lung disease, cancer, arthritis, and psychiatric problems) and demographics (sex, age, educational level, marital status, and household income) are used. Moreover, we estimate the total numbers of people who will be living with AD in 2020, 2030, 2040, and 2050 to predict the total annual cost of AD in future decades. Few large-scale national surveys of the monetary cost or economic burden of AD have been conducted in China, or indeed in Asia. To remedy this lack of data, we also systematically review COI studies of AD that report annual costs per patient. This will enable estimation of the proportion of the global burden of AD costs faced by China. Furthermore, it will enable comparison of the economic burden of AD in developed and developing countries.

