#### Sensitivity analyses

Sensitivity analyses will be conducted to examine the robustness of the results from the base case model and explore correlations between certain factors that could impact each other. First, the total costs of dementia will be estimated using the prevalence rates derived from a systematic review. Then the minimum and maximum salaries (rather than the average) will be used to estimate the relative costs. The total costs will be estimated by assuming that 70 and 99% of patients with AD are living at home, instead of 86% in the primary option. Furthermore, different costing caregiver time will be used to estimate the total cost. All of the analyses will be performed using R software version 3.2.3.

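### The treated share d weights every term of the national cost but is given only as 10–30%, and none of the listed sensitivity analyses varies it; the untreated-count formula also needs a notation correction

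*Protocol article*

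**What the plan says.** All references are to the Methods of the protocol article.

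- *Current total number of patients with AD in China* defines the treated share: "the percentage of AD patients who received anti-dementia treatment is defined as d" per cent. It then says that "the number of anti-dementia treated patients (M_1_) is M × d" per cent and that "the number of patients not treated for dementia (M_2_) is M × (1–d", with the bracket closed and the percent sign placed after it.
- The same section supplies the value of d as a range from earlier reports: "the percentage of AD patients who are treated for dementia is 10–30" per cent. It names no base value.
- *Nationwide cost due to AD* splits the treated count into inpatients and outpatients: "the number of patients who undergo treatment nationwide (M_1_) is multiplied by 1/7 or 6/7". It then states that "the total annual national cost of patients with AD is M_1_1_ x F_1_1_ + M_1_2_ x F_1_2_ + M_2_ x F_2".
- *Sensitivity analyses* lists prevalence from a systematic review, minimum and maximum salaries, the share living at home, and alternative costing of caregiver time. For the share living at home it gives a primary value of 86% and two bounds: "The total costs will be estimated by assuming that 70 and 99% of patients with AD are living at home". The treated share is not in the list.

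**The concern.** The abstract and the Results section name the national annual cost as one of two main findings. Through the counts of treated and untreated patients, d enters all three terms of that cost. The projections for 2020 to 2050 and the comparison with the global burden use the same construction and would inherit the choice of d.

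The article cites a threefold uncertainty in d and then lists robustness analyses that leave it out. An analyst who follows the list will report a range around the national figure that is conditional on one unstated value of d, and readers cannot see how much that value matters. The contrast with the share living at home is telling. That input is not a term in the national cost formula, yet it gets a primary value and two bounds.

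Separately, the printed expression for the untreated count does not give the complement of the treated count.

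**Working it through.** **Plan's own figure.** The article states no value for M in 2015, for either count, or for the national cost, so there is no figure on this point to reproduce.

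**Inputs.**
- d = 10 to 30 per cent (*Current total number of patients with AD in China*).
- M: no 2015 value is printed. For illustration only I use the 2010 count of 5.69 million from the same section ("the number of AD patients in China aged ≥ 60 years in 1990, 2000, and 2010 was 1.93 million, 3.71 million, and 5.69 million, respectively").
- Split of the treated count: 1/7 inpatient, 6/7 outpatient (*Nationwide cost due to AD*).
- F_1_1, F_1_2 and F_2: not given. I read them as average costs per patient, since they are multiplied by patient counts.
- r = (F_1_1/7 + 6·F_1_2/7) / F_2, the ratio of treated to untreated cost per patient. This is my assumption, taken from 0.5 to 5.

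**Step 1: the printed counts.** Take d as the number in front of the percent sign. M_2 is then (1 − 10)% = −9% of M at d = 10, −19% at d = 20 and −29% at d = 30. With M = 5.69 million that is −0.512, −1.081 and −1.650 million. The sum M_1 + M_2 is d% + (1 − d)% = 1% of M for any d. If d is a proportion instead, the counts are 0.1% and 0.9% of M at d = 0.1, and 0.3% and 0.7% at d = 0.3. The sum is again 1% of M. Neither reading recovers M.

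**Step 2: the evident intention.** With M_2 = M × (1 − d%) = M × (100 − d)%:

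| d | M_1 (million) | M_2 (million) | Sum |
|---|---|---|---|
| 10% | 0.569 | 5.121 | 5.69 |
| 20% | 1.138 | 4.552 | 5.69 |
| 30% | 1.707 | 3.983 | 5.69 |

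**Step 3: effect of d on the national total.** With d as a proportion, total cost = M × F_2 × (d·r + 1 − d). The ratio of the total at 30% to the total at 10% is (0.3r + 0.7) / (0.1r + 0.9). M and F_2 cancel.

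| Assumed r | Calculation | Change from d = 10% to d = 30% |
|---|---|---|
| 0.5 | 0.85 / 0.95 | −10.5% |
| 1 | 1.00 / 1.00 | 0% |
| 1.5 | 1.15 / 1.05 | +9.5% |
| 2 | 1.30 / 1.10 | +18.2% |
| 3 | 1.60 / 1.20 | +33.3% |
| 5 | 2.20 / 1.40 | +57.1% |

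The treated component alone triples (0.3r / 0.1r), but the untreated component falls at the same time, from 0.9 to 0.7 of M × F_2. The change in the total is the relevant figure.

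**Step 4: the direction of r.** *Per capita annual cost of AD patients* defines the untreated group as reporting neither outpatient nor hospital costs, which pushes r above 1. Total cost also includes formal care, informal care and other non-medical items, which untreated patients incur too, and the Discussion says that 84.9% of patients are cared for at home by non-professionals. These shared costs pull r towards 1. The article does not settle its value.

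**Step 5: the per-patient result.** *Total cost per patient per year* adds up each patient's own costs. It does not use d.

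**The case against.** Four arguments weigh against this point.

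First, the formula is a misplaced percent sign. Treated and untreated patients are plainly complements, and nobody would carry a negative number of patients into a cost calculation. This stands. A reader might infer from Step 1 that the untreated count is unusable or that the national cost will come out wrong. The text does not support that, because the intended expression is evident.

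Second, this is a condensed article. The base value of a literature input may sit in the full protocol or analysis plan, and the sensitivity list is not said to be exhaustive. This stands in part. The missing base value alone would be no more than omitted detail. But the article does print a list of sensitivity analyses, with a primary value and bounds for another input, and it cites a threefold range for d elsewhere without carrying that range into the list.

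Third, the size is unknown. This stands. Showing only r of 2 and above would suggest that the total must rise with d, whereas it does not move at r = 1 and falls at r = 0.5. A reader might also infer that d is among the largest uncertainties in the study. That cannot be said, because the effects of prevalence, salary, share living at home and caregiver-time costing have not been worked out for comparison.

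Fourth, the per-patient cost, the other main finding, does not depend on d. This stands and limits the scope.

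**Conclusion.** The point holds for the national cost only. The plan as written weights every term of that cost by a treated share known only to lie between 10% and 30%, and its listed sensitivity analyses do not vary that share. The effect of moving across the range is −10.5% at r = 0.5, nil at r = 1, +18% at r = 2, +33% at r = 3 and +57% at r = 5. All of these r values are assumed. The calculation also rests on reading the untreated count as the complement of the treated count and the F terms as per-patient averages.

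This should be fixed, but it does not invalidate the design or the per-patient estimates. The formula error is one of notation. It may be tempting to conclude that d will be picked after the costs are seen. The article does not say so. It only leaves that possibility open by not stating a value.

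**What to change.** 1. In *Current total number of patients with AD in China*, state one base value of d, with its source, before the costs are analysed. The documents give no ground for preferring any particular value within the range, so the sponsor should justify the choice.
2. In *Sensitivity analyses*, add the national total at d = 10% and at d = 30%, and report that range beside the main national figure.
3. Print the untreated count as M × (1 – d%), or equivalently M × (100 – d)%, so that M_1 + M_2 = M.
4. While making these edits, check that the groups match. d counts patients on anti-dementia treatment, whereas F_2 comes from patients who reported neither outpatient nor hospital costs.

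The first three changes cost one stated input, two further runs of an existing calculation and one corrected expression, and need no new data. The downside is a possibly wider range around the national figure.

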#### Per capita annual cost of AD patients (who accepted or did not accept treatment)

The cost associated with treating dementia patients (F_1_) is divided into two groups: “outpatient costs” and “hospitalised or inpatient costs.” F_1_1_ is defined as the average annual cost in the inpatient group (average annual cost × the number of inpatients annually), and F_1_2_ is the average annual cost in the outpatient group (average annual cost × the number of outpatients annually). Patients described as not accepting treatment are those who did not select either “outpatient service costs” or “hospitalised costs” in their questionnaire. F_2_ is defined as the average annual cost per AD patient who did not accept treatment.

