### Sample size

The sample size was calculated using the equation, $$ n=\frac{U_{1-\alpha /2}^2{S}^2}{\delta^2} $$ where *S* was the stand division and *δ* was the allowable error. The planned sample size was generated based on previous data obtained from an economic evaluation of an AD-type dementia study [26]. Based on the standard deviation (SD) of AD-related costs per patient per year (11,037) and an allowable error of 500, the total sample size required was 1,872. Therefore, the planned total sample size in this study was ~2,500 to allow for a defective rate of 25%. Before starting the study, information was surveyed from all randomly selected participating sites, including the number of dementia physicians at each site, the number of AD patients, and the proportion of outpatients and inpatients in the last year. Based on these data 20–40 patients with AD will be assigned for each site. The sites include hospitals (Tier 3 hospitals, gerontology hospitals, mental health centres and psychiatric hospitals), nursing homes, gerocomiums, care facilities, and residences.

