### Quality control

The questionnaire and standard operating standards procedures were formulated based on previous studies and by consulting relevant experts internationally and domestically. All of the staff working on this study were trained to ensure that standard operating procedures were followed, and all of them were required to pass an examination before beginning data collection. A pilot study was conducted in five randomly selected hospitals and residences to evaluate the feasibility and reliability of the questionnaire and to identify any potential problems.

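### The inpatient and outpatient cost terms are defined as group totals and then multiplied by national headcounts, so patient numbers enter the treated part of the national cost twice

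*Protocol article*

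**What the plan says.** The section of the protocol article headed "Per capita annual cost of AD patients (who accepted or did not accept treatment") sets up three cost terms.

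- Inpatients: "F_1_1_ is defined as the average annual cost in the inpatient group (average annual cost × the number of inpatients annually").
- Outpatients: "F_1_2_ is the average annual cost in the outpatient group (average annual cost × the number of outpatients annually").
- Untreated patients: "F_2_ is defined as the average annual cost per AD patient who did not accept treatment". These are the patients who ticked neither the outpatient nor the hospital cost item in the questionnaire.

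The section on nationwide cost then states that "the total national annual cost of patients who accept treatment is M_1_1_ × F_1_1_ + M_1_2_ × F_1_2", and adds M_2 × F_2 for untreated patients. M_1_1 and M_1_2 are national patient numbers, obtained as 1/7 and 6/7 of all treated patients (M_1). The split rests on a pilot finding that "the average annual ratio of inpatients to outpatients in different hospitals is ~1:6".

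The Results section names the national annual cost as one of the two main findings. The Sensitivity analyses section varies prevalence, salaries, the share of patients living at home and the costing of caregiver time. It does not vary the 1:6 ratio.

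**The concern.** A formula of the form national headcount × F gives a national cost only if F is a cost per patient. The bracketed definitions make F_1_1 and F_1_2 something else: a mean already multiplied by a number of patients. They conflict with the section's own heading, with the word used for them in the same sentence, and with F_2, which is handled correctly. An analyst who follows the brackets gets a treated cost in currency × patients and is then told to add it to an untreated cost in currency.

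The same formula carries a second ambiguity. M_1_1 and M_1_2 divide the treated population exactly, so the two means should come from groups divided in the same way. The questionnaire wording leaves room for one patient to report both kinds of cost, and the article does not say where that patient is counted.

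At stake are the national total and the projected costs for 2020 to 2050, which build on it.

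**Working it through.** **1. The plan's own figure.** A ratio of 1:6 gives 1/(1+6) = 1/7 and 6/(1+6) = 6/7, which sum to 1. The stated split is arithmetically correct.

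**2. Units.** Let c_in and c_out be mean annual cost per patient, and n_in and n_out the patient numbers in the brackets.

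- As written: M_1_1 × (c_in × n_in) + M_1_2 × (c_out × n_out), in currency × patients.
- With per-patient means: M_1_1 × c_in + M_1_2 × c_out = M_1 × (c_in/7 + 6 × c_out/7), in currency.
- Untreated: M_2 × F_2, in currency. It can be added only to the second form.

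**3. Size on a literal reading.** Assume c_in = c_out, so that only the extra factor shows, and n study patients split 1:6. The factor is (1/7)(n/7) + (6/7)(6n/7) = 37n/49.

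- n = 1,872 (required size, Sample size section): 37 × 1,872/49 ≈ 1,414.
- n = 2,500 (planned size): 37 × 2,500/49 ≈ 1,888.

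The article does not say which annual number of patients the brackets mean, so the factor is not fixed.

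**4. One group per patient.** The Direct medical costs section collects outpatient visits over 3 months and hospital stays over 12 months. The untreated group is those who selected neither item. Nothing in this wording stops a patient from reporting both. To illustrate, suppose the 1:6 ratio counts such patients on both sides, a fraction v of inpatients are also counted as outpatients, and an inpatient costs r times an outpatient-only patient (all assumed).

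- Correct treated mean: (r + 6 − v)/(7 − v).
- Mean when these patients enter both groups: (r + v × r + 6 − v)/7.
- r = 2, v = 0.5: 1.214 against 1.154, about 5% too high.
- r = 5, v = 1: 2.143 against 1.667, about 29% too high.

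**5. The fixed ratio.** Set outpatient cost to 1 and inpatient cost to q = 5 (assumed). With inpatient share s, the treated mean is T = 5s + (1 − s).

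| Ratio | s | T | Change |
|---|---|---|---|
| 1:6 | 1/7 | 1.571 | – |
| 1:3 (assumed) | 1/4 | 2.000 | +27% |
| 1:10 (assumed) | 1/11 | 1.364 | −13% |

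For the national total, take the treated share d = 10% to 30% from the section on the total number of patients, and assume that untreated cost equals outpatient cost. The mean over all patients is d × T + (1 − d).

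- d = 10%: 1.057 at 1:6; 1.100 at 1:3 (+4%); 1.036 at 1:10 (−2%).
- d = 30%: 1.171 at 1:6; 1.300 at 1:3 (+11%); 1.109 at 1:10 (−5%).

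**The case against.** The best reply is that the brackets are a drafting slip. The heading, the description of both terms as averages, the per-patient F_2 and the definition of total cost per patient per year all point to a per-patient mean, and with such means the national formula is dimensionally sound. The bracket may be a garbled form of unit cost × frequency, since the questionnaire collects the cost of the last visit or stay and the number of each. That reading is plausible, but the text says number of inpatients and number of outpatients, in both definitions. The reply lowers the likely effect on the result; it still concedes that the definitions must be rewritten.

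A second reply is that the two groups may well be exclusive in practice. The text speaks of dividing into groups, and the Data collection procedure identifies patients by source. A reader might infer that the groups do overlap; the documents do not say so. They only leave it possible, and a detailed assignment rule may sit in the fuller protocol. What stands is that the two means must match a split that sums to 1.

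A third reply concerns the source of the ratio. The Quality control section says "A pilot study was conducted in five randomly selected hospitals and residences", to test the questionnaire, and a reader might infer that 1:6 comes from those five sites and is weaker than the pre-study survey. The article never ties the ratio to that pilot. Nor is the survey shown to be a full substitute: it recorded for each site "the number of AD patients, and the proportion of outpatients and inpatients in the last year", which need not distinguish patients who were both. That objection stands. What remains is that the ratio is held fixed while other inputs are varied.

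**Conclusion.** The formula for the treated part of the national cost is wrong as written. F_1_1 and F_1_2 are defined as group totals, headcount enters twice, and the result cannot be added to M_2 × F_2. This follows from the text alone and needs no assumption.

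The factor of roughly 1,400 to 1,900 depends on equal means and study counts. It shows what the literal definition would do. A reader might infer that the reported national cost will be inflated on that scale, but the surrounding wording makes a per-patient mean the likely intention, so the documents do not support that inference.

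The other two parts are smaller and conditional. Counting patients in both groups would raise the treated mean by about 5% to 29% under the assumed inputs. Moving the ratio to 1:3 or 1:10 shifts the treated mean by +27% or −13%, but the national total only by about +4% to +11% or −2% to −5%, because 10–30% of patients are taken as treated. These figures assume a fivefold inpatient cost and an untreated cost equal to outpatient cost; a lower untreated cost would make the shifts in the total larger.

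**What to change.** 1. Delete the bracketed multiplications. Define F_1_1 and F_1_2 as mean annual total cost per patient in the inpatient and outpatient groups, parallel to F_2. The national formula can then stay as it is.
2. State that each treated patient is counted in one group only when the two means are computed, so that the groups match the 1/7 and 6/7 split.
3. Add a sensitivity analysis that varies the 1:6 ratio over the range of inpatient and outpatient proportions recorded by the pre-study site survey.

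The first two are changes of wording plus one classification step in the analysis. The third uses site information that the article says was already gathered, and needs a recalculation of the national total only. None of this requires patient-level data from the survey.

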#### Direct medical costs

The direct medical costs include outpatient costs, hospitalisation costs, and out-of-pocket expenses for healthcare medications. Outpatient costs include the reason for the visit (due to AD, AD-related symptoms, or comorbidities), the number of outpatient visits in the past 3 months, and the cost of the last clinic visit in the same 3-months period. The cost of clinic visits includes registration (general physicians or specialists), diagnostic procedures (e.g., consultation, scale evaluation), imaging (e.g., CT, MRI, SPECT, and PET), laboratory tests, medication, and non-drug treatment (such as rehabilitation treatment). The outpatient medication costs are divided into three categories: anti-dementia drugs, medications for the treatment of AD-related symptoms (e.g., sleep disorders, psychiatric symptoms, and gastrointestinal symptoms caused by medications), and the treatment of comorbidities. For anti-dementia drugs the specific medications used and their corresponding costs are also investigated. For comorbidity-associated costs, the types of comorbidity and the associated costs are recorded. Investigations into the cost of hospitalisation included the reason for hospitalisation (AD, AD-related symptoms, or comorbidities), how many times a patient was hospitalised in the past 12 months, and expenditures on the last hospitalisation within the past 12 months. The hospitalisation expenditure includes the cost of the ward bed, formal care, examinations, laboratory tests, treatment (such as rehabilitation, massage, and others), and medications. The term “self-bought medications” means that the patient or their caregivers purchased the medications outside the hospital (out-of-pocket spending). Questions include how many times medications were purchased in the past month and the total expenditure during the same period. The above data also include information regarding the patients’ payment method (including medical insurance for urban workers or town residents, rural cooperative medical insurance, commercial insurance and self-funded) and any out-of-pocket expenses.

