### Data collection procedure

Electronic medical record systems are being used to identify elderly patients diagnosed with AD among outpatients (in the last 3 months), inpatients (in the last 12 months), those living in urban residences and rural residences with their families, and residents of nursing homes, gerocomiums, or care facilities. The diagnosis of AD is re-confirmed by dementia specialists before the start of the study. The intensive dementia training program conducted in national and regional centres included both theory and practice. It comprised the study methods, assessment of the scales and internationally accepted diagnostic criteria of dementia and its subtypes, neuroimaging (CT and MRI), and standard procedures for diagnosis. Investigators are contacting patients and re-confirm the accuracy of the AD diagnosis according to the inclusion and exclusion criteria. Neuroimaging and laboratory tests will be performed when necessary. New patients are also being enrolled during the study period. Face-to-face questionnaires will be administered to AD patients and their caregivers when the data and information could not be collected through electronic medical record or residence health systems. The surveys are being administered by investigators to ensure the accuracy of the diagnosis and data.

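### Treatment status for the annual costs F_1_2 and F_2 rests on a 3-month outpatient window and a 12-month hospital window, so some patients who attended within the year count as untreated

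*Protocol article*

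**What the plan says.** Under Direct medical costs, the outpatient questions cover "the number of outpatient visits in the past 3 months, and the cost of the last clinic visit in the same 3-months period". The hospital questions cover "how many times a patient was hospitalised in the past 12 months, and expenditures on the last hospitalisation within the past 12 months". The Data collection procedure uses the same two windows to find patients: "outpatients (in the last 3 months), inpatients (in the last 12 months".

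Under Per capita annual cost of AD patients, a patient is untreated if neither item was selected: "Patients described as not accepting treatment are those who did not select either “outpatient service costs” or “hospitalised costs” in their questionnaire". The mean for that group is then treated as a yearly figure: "F_2_ is defined as the average annual cost per AD patient who did not accept treatment".

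On annualisation, Total cost per patient per year says only this: "All of the costs will be converted into the average annual cost". Under Nationwide cost due to AD, F_1_2 is multiplied by the number of treated outpatients and F_2 by the number of untreated patients. Both counts come from outside the survey sample: a literature-based patient total and treated share d, and a pilot ratio of inpatients to outpatients.

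**The concern.** A status meant to hold for a year is read from two items with different look-back periods. Take a patient with no admission in the past 12 months whose last clinic visit was 4 months ago. That patient has nothing to enter under outpatient costs and is classed as not accepting treatment. Interviewed two months earlier, the same patient would have been an outpatient. Group membership thus depends partly on interview date and visit spacing.

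The stake is the national total, one of the two main results. It is built from group means weighted by external counts, so moving patients between groups changes the means without any offsetting change in the weights.

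**Working it through.** **Is there a repair elsewhere in the article?**

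- Converting costs to a yearly basis rescales amounts. It cannot move a patient from one group to another.
- The Sensitivity analyses vary prevalence, salaries, the share living at home and the costing of caregiver time. None varies treatment status.
- No 12-month outpatient question is described.

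**Who is exposed?** Only patients with no admission in 12 months. Those found in the records as outpatients of the last 3 months mostly have a visit in the window. That leaves chiefly patients from residences, nursing homes and care facilities.

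**Inputs.** From the article: windows of 3 and 12 months; d = 10–30%, so the untreated count M_2 is 70–90% of all patients; outpatients are 6/7 of the treated. The article gives no visit rate, no share of the sample without any visit in the year, and no misclassification figure to reproduce. Those inputs below are assumptions.

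**Share misclassed.** With Poisson visits at r per year, among non-hospitalised patients with at least one visit in 12 months:

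P(no visit in 3 months | at least one in 12) = (e^(−r/4) − e^(−r)) / (1 − e^(−r))

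For r = 2: (0.607 − 0.135) / 0.865 = 0.545.

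**Effect on F_1_2.** If 3-month visits are multiplied by 4, the mean among those classed as outpatients is r / (1 − e^(−r/4)). The true mean among 12-month attenders is r / (1 − e^(−r)). The overstatement factor for visits is the ratio, (1 − e^(−r)) / (1 − e^(−r/4)). For r = 2: 5.08 / 2.31 = 2.20.

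**Make-up of the F_2 group.** If a share u of non-hospitalised patients truly had no visit in 12 months and m is the misclassed share, attenders form (1 − u)m / [(1 − u)m + u] of the group. The last column uses u = 0.5.

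| Visits per year | Misclassed | F_1_2 visit factor | Attenders in F_2 group |
|---|---|---|---|
| 1 | 65% | 2.86 | 39% |
| 2 | 55% | 2.20 | 35% |
| 4 | 36% | 1.55 | 26% |
| 6 | 22% | 1.28 | 18% |
| 12 | 5% | 1.05 | 5% |

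Over u = 0.2 to 0.8 and 1 to 12 visits, the last column ranges from 1% to 72%.

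With evenly spaced visits, k per year, the misclassed share is max(0, 1 − 3k/12): 75%, 50%, 25% and 0% at k = 1, 2, 3 and 4.

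**Effect on the national total (outpatient and untreated terms only).** Per patient, this part of the total is d × 6/7 × F_1_2 + (1 − d) × F_2. Assume a cost of 1 unit per visit, 2 or 4 visits a year, u = 0.5 and d = 10–30%. Let all other costs be 20 or 10 units.

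- Other costs equal (20 and 20). For 2 visits and d = 10%: F_1_2 goes from 22.31 to 25.08 and F_2 stays at 20. The sum goes from 0.1 × 6/7 × 22.31 + 0.9 × 20 = 19.91 to 20.15, a rise of 1.2%. Across scenarios the rise is 1% to 4%, all of it through F_1_2.
- Attenders 20, untreated 10: rises of 18% to 31%, mainly because F_2 goes up (10 to 13.53 at 2 visits).
- Attenders 10, untreated 20: falls of 7% to 15%, because F_2 goes down (20 to 16.47 at 2 visits).

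**The case against.** The questionnaire is not shown. That its outpatient cost item carries the 3-month window is an inference, though 3 months is the only outpatient window in the article. This limits certainty but does not remove the point.

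A short recall period for clinic visits is ordinary practice, and multiplying a 3-month count by 4 is unbiased for a whole-sample mean under steady attendance. That stands for the per-patient annual cost and the GLM, neither of which uses this classification. It does not rescue the group means, because here the window also decides who is in each group.

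A reader might infer several stronger things that the documents do not support:

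- That F_2 is wrong because attenders enter it with no outpatient cost. A truly untreated patient has no outpatient cost either. F_2 moves only if the misplaced attenders differ in self-bought medication, non-medical or caregiver costs, and the article does not say how they differ.
- That a weight of 70–90% makes the error in the national total large. The weight applies to whatever shift F_2 has, and that shift could be nil.
- That the misclassed share is simply e^(−r/4), which is 61% at 2 visits a year. That counts patients with no visit all year, who are correctly called untreated; the conditional figure is 55%.
- That every non-hospitalised outpatient is at risk. Recruitment from 3-month outpatient records protects many of them.
- That M_2 is by definition a 12-month count of people with no visit. It is derived from the share receiving anti-dementia treatment, with no period stated.

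**Conclusion.** The point holds: as written, the rule puts some patients who attended within the year into the group whose mean is called the annual cost of untreated patients, and nothing shown corrects it. F_2 is a mixture whose bias has no determinable sign. F_1_2 tends to be overstated if 3-month use is multiplied up to a year. The damage is confined to the split behind the national total and anything built on that split.

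Its size cannot be computed from the article. The misclassed share falls from about 65% to 5% between 1 and 12 Poisson visits a year, and from 75% to 0% between 1 and 4 evenly spaced visits. The change in the national total was 1% to 4% upward when other costs were equal. It ran from about −15% to +31% when they were assumed to differ twofold, so those wider figures illustrate sensitivity and are not estimates. All of this rests on the outpatient item using the 3-month window. It should be corrected before the national total is reported.

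**What to change.** 1. Define treatment status over one common 12-month window. Take a 12-month outpatient yes/no or visit count from the electronic record already used to identify patients, or from one added question.
2. Count only visits and admissions for AD or AD-related symptoms. The reason for each is already among the items collected, and the added 12-month item should be limited in the same way. Otherwise the longer window would move patients who attended only for comorbidities into the treated group.
3. Keep the 3-month cost recall. Average the annualised outpatient cost over all 12-month attenders, with zero for those who had no visit in the window. Under the Poisson model this gives 4 × (r/4) / (1 − e^(−r)) = r / (1 − e^(−r)) visits, which is the true mean for attenders. Costing the visits in months 4–12 directly is not feasible, because only the last visit within 3 months is priced.
4. Report F_1_2, F_2 and the national total under both the 12-month definition and the one now in the protocol.

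The cost is one record field or one question per patient, plus a second run of the national calculation. The downside is somewhat more recall error for a 12-month item where no record exists.
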